### Randomisation and allocation concealment

We will use the stratified block randomisation method to perform randomisation. A random number sequence will be automatically generated by R V.4.0.3 (R Foundation for Statistical Computing, Vienna, Austria) before the inclusion of the first participants. Gender is first used as a stratification factor, and 36 cases of each gender will be included, and then block group randomisation will be performed for each gender, with block group lengths set to 2–8 and randomly selected by the computer.

To perform allocation concealment, we will seal the randomisation list in sequentially numbered opaque envelopes. The envelopes will be opened sequentially at the beginning of the intervention in the order of entry, and the grouping of participants will be determined according to the allocation scheme inside the envelope.

### Blinding

By using identical doses and appearance of HMB-enriched nutritional supplements and placebos, participants and outcome assessors will be blinded to group allocation.

### Interventions

The participants will be randomly assigned into two groups: the intervention group and the control group. The two groups will be randomly labelled A or B. The participants in both groups will perform a calorie restriction diet. They will receive individualised nutritional guidance from professional dietitians by video regarding calorie restriction strategies. The principle for calorie restriction will be based on the equation: energy intake=ideal BW (ie, height (cm)−105)×25 kcal/kg/day.^23^ The compliance will be followed via a WeChat group and telephone. The intervention duration in both groups will be 12 weeks.

#### Intervention group

The participants in the intervention group will receive oral HMB-enriched nutritional supplements (65 g, once daily) in powder form packaging in opaque plastic bottles, which include soybean isolate, protein, whey protein, casein, HMB, L-glutamine, wheat oligopeptide, medium-chain fatty acids, vitamin D, vitamin E, konjac powder and fish oil powder.

#### Control group

The participants in the control group will receive a placebo (maltodextrin 65 g once daily) in powder form packaging in the same opaque plastic bottles as the intervention.

### Outcomes

As shown in table 1, the assessors, who will be blinded to the group allocation, will ask the participants to complete the questionnaires (including demographic characteristics, physical activity and energy intake), anthropometric measurements (including BW, height, waist circumference and hip circumference), heart rate, blood pressure, hand grip strength (HGS) measurement, sit-to-stand test and body composition at the baseline, the 6-week intervention and the end of the 12-week intervention. Additionally, participants will complete the self-reported questionnaires at the 3 and 9 weeks.

Moreover, fasting blood will be taken by a nurse at baseline and at the end of the 12-week intervention after intervention for laboratory analysis of biomarkers of glucose metabolism (fasting glucose and insulin), albumin, haemoglobin, alanine aminotransferase (ALT), aspartate aminotransferase (AST), gamma-glutamyl transpeptidase (GGT), cystatin C, creatinine, estimated glomerular filtration rate (eGFR), lipid profiles and full blood counts. The fasting blood will be sent to the clinical laboratory of West China Hospital, Sichuan University, within 2 hours after withdrawal. These biomarkers will be tested using standard methods. Moreover, the homeostasis model assessment of insulin resistance (HOMA-IR) will be calculated using the equation: fasting glucose (mg/dL)×fasting insulin (μIU/mL)/405.

#### Primary outcome

The mean change in whole-body skeletal muscle mass (SMM) from the beginning to the end of the 12-week intervention will be measured for all participants. The whole-body lean body mass will be measured by trained research staff using a bioimpedance analysis device (BIA; InBody 770; Biospace, Seoul, Korea). The participants will be guided through the BIA test. They will be asked to stand upright at least 5 min before testing, then to step on the footplate barefoot with their heels on the rear sole electrodes and their hand holding the hand electrode. Their arms should be straight and should not touch the side of the body during the test.

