**Trial registration number:**

NCT04953936.

Strengths and limitations of this studyThis is the first randomised, double-blind, placebo-controlled trial to explore the possible effectiveness and safety of β-hydroxy-β-methylbutyrate (HMB)-enriched nutrition supplements for maintaining skeletal muscle mass and function in obese adults during calorie restriction.Using identical doses and appearance of HMB-enriched nutritional supplements and placebos to mask participants and outcome assessors.The hydration status of the participants may affect the results of the bioimpedance analysis.The sample size of this trial is relatively small.

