**Figure 1 F1:**
[figure not shown]
Flow chart of this trial. HMB, β-hydroxy-β-methylbutyrate.

**Table 1 T1:** Schedule of enrolment, interventions and assessments

Timepoint	Enrolment	Allocation	Postallocation			
	Visit 1	Visit 2	Visit 3	Visit 4	Visit 5	Visit 6
	Screening (−4 to 0 week)	Baseline (0 week)	3 weeks±2 days	6 weeks±2 days	9 weeks±2 days	12 weeks±2 days
Enrolment						
Consent	√					
Inclusion and exclusion	√					
Demographics	√					
Medical history	√					
Body height	√					
Body weight	√					
Blood pressure	√					
Heart rate	√					
BIA	√					
Allocation		√				
Interventions*						
HMB nutritional supplement+calorie restriction						
Placebo+calorie restriction						
Assessments						
Inclusion and exclusion		√				
Body weight		√		√		√
Blood pressure		√		√		√
Heart rate		√		√		√
WC		√		√		√
HC		√		√		√
IPAQ-SF		√	√	√	√	√
FFQ		√	√	√	√	√
BIA		√		√		√
Sit-to-stand test		√		√		√
HGS		√		√		√
Blood tests†		√				√
Adverse events‡			√	√	√	√
Adherence‡			√	√	√	√

*Both intervention groups will also receive dietary instruction.

†The blood tests will include glucose metabolism (fasting glucose and insulin), albumin, haemoglobin, alanine aminotransferase, aspartate aminotransferase, gamma-glutamyl transpeptidase, cystatin C, creatinine, estimated glomerular filtration rate, lipid profiles and full blood counts.

‡Weekly WeChat or telephone contacts will be performed to assess adverse events and adherence (including dietary compliance).

BIA, bioimpedance analysis; FFQ, Food Frequency Questionnaire; HC, hip circumference; HGS, hand grip strength; HMB, β-hydroxy-β-methylbutyrate; IPAQ-SF, International Physical Activity Questionnaire Short Form; WC, waist circumference.

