### Participants

#### Inclusion criteria

Individuals who meet all the following criteria will be invited to participate in this study: (1) men and women aged 30–50 years; (2) currently having obesity defined by BMI ≥28 kg/m^2^ (based on measured body weight (BW) and height at booking using validated scales)^21^; (3) having an intention to lose weight via calorie restriction; (4) healthy and able to walk independently; (5) able to eat independently to meet their energy needs; (6) without significant BW change in the last 6 months (less than 5% change in BW); (7) having sedentary habit defined by Sedentary Behavior Research Network^22^; (8) able to collaborate with the research staff. Individuals will be recruited by research nurses or physicians. The study protocol will be provided in advance and individuals who wish to participate will be offered the opportunity to discuss the study and consent to participate. All participants will be required to sign the written informed consent before participation.

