### Statistical analysis plan

The statistical analysis will be performed by an independent statistical expert blinded to the group allocation. SPSS V.26.0 (IBM) and R V.4.0.3 (R Foundation for Statistical Computing, Vienna, Austria) will be used for statistical analysis.

Each group will be summarised in terms of demographic characteristics and baseline variables. For comparisons of continuous variables, two-sample t-tests or Mann-Whitney U tests will be used, whereas for categorical variables, the χ^2^ test or Fisher’s exact test will be used.

As aforementioned, the primary outcome will be in SMM from the beginning to the end of the 12-week intervention. The independent two-sample t-test or Mann-Whitney U test will be used based on the distributional normality. We will make adjustments based on the covariates if there are significant demographic differences between the groups or if baseline variables differ significantly. In the primary analysis, the full analysis set (FAS) will be the main data set. Participants initially assigned to either group will be included in the FAS. However, our analysis will not use the data of ineligible participants (ie, those who are wrongly enrolled because of measurement or human error), subjects who received less than 75% of the planned intervention or subjects without the primary outcome measurement. For sensitivity analysis, we will use a protocol-specific set to compare with the results from the FAS. A per-protocol analysis will include participants who achieved the completion of the study without major deviations from protocol, who provided the primary outcome and who received at least 75% of the planned intervention. The rate of protocol compliance in each group will be calculated. A significance level of two-sided p<0.05 will be used. If needed, the multiple imputation method will be adopted for missing data.

We will use the same methods for analysing secondary outcomes as we did for analysing the primary outcome. A paired t-test or Wilcoxon signed-rank test will be used to assess the changes in outcome measures within groups before and after the intervention. To validate trend differences per visit, we will use repeated measures analysis of variance with post hoc tests.

Moreover, subgroup analysis will be done to identify whether gender or Asian Working Group on Sarcopenia-defined sarcopenia^30^ at baseline would affect the clinical response to HMB-enriched nutritional supplements.

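### The screening BIA reading has no stated analytic role; prespecifying it as a second baseline covariate could add a little precision at almost no cost

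*Protocol article*

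**What the plan says.** In the Protocol article, Table 1 ("Schedule of enrolment, interventions and assessments") ticks BIA in the enrolment block at Visit 1, headed "Screening (−4 to 0 week", and again in the assessment block at Visits 2, 4 and 6. Each participant is therefore due two BIA readings before treatment starts.

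The Outcomes section lists "body composition at the baseline, the 6-week intervention and the end of the 12-week intervention" and does not mention screening. The Primary outcome section defines "The mean change in whole-body skeletal muscle mass (SMM) from the beginning to the end of the 12-week intervention". It does not say which visit the beginning is; that it means Visit 2 follows from the Outcomes section.

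Under Statistical analysis plan, the test is fixed as follows: "The independent two-sample t-test or Mann-Whitney U test will be used based on the distributional normality". Covariates enter only conditionally: "We will make adjustments based on the covariates if there are significant demographic differences between the groups or if baseline variables differ significantly". The limitations paragraph of the Discussion adds that recorded physical activity and energy intake will be adjusted for. None of these statements involves the screening reading.

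No inclusion or exclusion criterion uses a BIA value; obesity is defined by BMI from weight and height. The article also lists as a limitation that "The hydration status of the participants may affect the results of the bioimpedance analysis", and it calls its sample relatively small.

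**The concern.** A change score carries the measurement error of its single baseline reading in full. Here a second pre-allocation reading of the same variable appears to be scheduled already, and the article neither assigns it a purpose nor uses it. Because both readings precede allocation, using the second one cannot bias the comparison of arms. What is at stake is precision in a trial that names its small sample as a weakness, and that takes its assumed effect from a different population (prefrail older adults). The gain would matter most if that effect proves optimistic here.

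**Working it through.** **Inputs from the article.** BIA at Visits 1, 2, 4 and 6; screening window of −4 to 0 weeks; 72 participants, 1:1; 25% attrition; standardised effect 0.93; two-sided 5% level.

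**Inputs assumed, because the article gives no SD.** True 12-week change SD d = 0.6 to 1.0 kg; single-scan error SD e = 0.3 to 0.7 kg; between-person SD s = 5 kg; SD g of true drift in skeletal muscle mass (SMM) between Visits 1 and 2 = 0 to 0.7 kg; correlation r of the Visit 1 and Visit 2 errors = 0 or 0.5. Change and drift are taken as independent of level.

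**The plan's own figure.** For effect 0.93 and 80% power the t-test needs 20 per arm, 40 in total, and 40/0.75 gives 54, not the stated 70. (At 90% power it needs 26 per arm, and 52/0.75 gives 70.) That is a separate matter. Here it only fixes the evaluable number: 72 × 0.75 / 2 = 27 per arm.

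**Step 1: change score.**
- One baseline scan: d² + 2e².
- Mean of two scans: d² + e² + e²(1 + r)/2 + g²/4.
- Saving: e²(1 − r)/2 − g²/4. It is positive only if g² < 2e²(1 − r), that is, drift variance below twice the error variance when errors are independent, and a lower limit when they are correlated.
- At d = 0.8, e = 0.5, g = 0, r = 0: 0.64 + 0.50 = 1.14 against 0.64 + 0.375 = 1.015, a fall of 11.0%.

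**Step 2: ANCOVA of week-12 SMM.**
- Visit 2 as the only covariate: residual variance = s² + d² + e² − s⁴/(s² + e²). At 0.8 and 0.5: 25.89 − 625/25.25 = 1.1375. This is only 0.2% below the change score, so the gain below comes from the second reading and not from ANCOVA as such.
- Both readings as covariates: residual variance = s² + d² + e² − c′S⁻¹c. Here c = (s², s²), and S has diagonal s² + e² (Visit 2) and s² + g² + e² (Visit 1) and off-diagonal s² + r·e². At 0.8 and 0.5 with g = 0, r = 0: 25.89 − 625/25.125 = 1.0144, a fall of 10.8%.

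**Step 3: drift and correlated errors.** Percentage fall in variance, each method against its own one-scan version (negative = loss of precision):

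| d / e (kg) | Method | g=0, r=0 | g=0.5, r=0 | g=0.7, r=0 | g=0, r=0.5 | g=0.7, r=0.5 |
|---|---|---|---|---|---|---|
| 1.0 / 0.3 | mean of two | 3.8 | −1.5 | −6.6 | 1.9 | −8.5 |
| 1.0 / 0.3 | both as covariates | 3.8 | 1.6 | 1.0 | 1.9 | 0.3 |
| 0.8 / 0.5 | mean of two | 11.0 | 5.5 | 0.2 | 5.5 | −5.3 |
| 0.8 / 0.5 | both as covariates | 10.8 | 7.2 | 5.5 | 5.4 | 1.8 |
| 0.6 / 0.7 | mean of two | 18.3 | 13.6 | 9.1 | 9.1 | 0.0 |
| 0.6 / 0.7 | both as covariates | 17.9 | 14.2 | 11.9 | 8.9 | 4.4 |

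Both as covariates never loses, because the regression gives the older reading less weight when it is less informative. The figures exclude the cost of the extra covariate. With 54 evaluable participants, and intercept, treatment, gender and Visit 2 already in the model, about 54 − 4 = 50 degrees of freedom remain, so one more costs roughly 1/50, or 2%, of variance. Gains below about 2% are therefore nil in practice.

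**Step 4: power at 27 per arm.** For variance cuts of 3.8%, 11.0% and 18.3%, before drift and the degree of freedom: at effect 0.93, 91.8% becomes 92.8%, 94.5% and 96.0%; at effect 0.5 (assumed), 43.8% becomes 45.2%, 48.1% and 51.4%.

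**The case against.** The strongest reply is that nothing here is wrong. Change from the baseline visit is a valid, ordinary endpoint, and how a baseline is derived from several readings is often left to an analysis plan, which is not shown. That stands as to severity: this is an improvement, not an error. It does not remove the point, because the article itself fixes the primary change, its test and a conditional rule for covariates, and none of these uses the second reading.

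A reader might infer more than the documents support:

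- **That the two scans are near-replicates and can simply be averaged.** The entry criterion "without significant BW change in the last 6 months (less than 5% change in BW" looks back from enrolment. It does not govern the gap to baseline, and 5% of an illustrative 80 kg is 4 kg, well above the assumed scan error. Participants intend to lose weight, and the article does not say that none begins before Visit 2. At a four-week gap drift may enter; at a gap near zero the two scans may share one hydration state.
- **That the screening reading is discarded.** The article only gives it no role.
- **That the protocol says hydration varies from one occasion to the next.** It says that hydration may affect the result, and the Discussion cites a study finding the device as accurate as DXA.

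It is also inferred, not stated, that Visit 1 uses the device and procedure described for the primary outcome; Table 1 says only BIA.

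**Conclusion.** The point holds as a low-severity, missed efficiency gain. A pre-allocation BIA reading is scheduled, serves no listed eligibility criterion and has no stated part in the primary analysis. There is no bias, contradiction or invalid test, and the documents would not support a claim of one.

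The size cannot be fixed from the documents. Under the assumed SDs, residual variance falls by about 4% to 18% with no drift and independent errors. With drift SD of 0.5 to 0.7 kg or correlated errors the gain shrinks, and where scan error is small it is close to zero. At the design's own effect size even the favourable cases add only about one to four points of power (91.8% to between 92.8% and 96.0%). If the true effect is nearer 0.5, the gain is at most about eight points (43.8% to 51.4%), which would not rescue the trial.

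**What to change.** Name Visit 2 as the baseline for the change score. Prespecify the primary analysis as an ANCOVA of week-12 SMM, or its change, on treatment, with the Visit 2 SMM, the Visit 1 SMM and the gender stratum as covariates, whether or not the arms differ at baseline. State a standard missing-covariate method for participants without a Visit 1 value. Confirm that Visit 1 uses the same device and procedure as Visit 2; if it does not, leave the Visit 1 value out.

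Do not replace the baseline by the mean of the two scans unless drift can be argued to be small by the condition in Step 1. Averaging would also let change before the intervention enter the planned within-group before-and-after tests.

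The cost is a few sentences, one degree of freedom and slightly more analysis work. No new visit, measurement or participant is needed.

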#### Secondary outcomes

We will measure the following secondary outcomes:

The mean change in appendicular skeletal muscle mass, trunk skeletal muscle mass, total body fat mass (BFM), appendicular body fat mass, trunk body fat mass, basal metabolic rate, phase angle and BW from the beginning to weeks 6 and 12, as well as the mean change in whole-body SMM from the beginning to week 6, will be measured for all participants. These data will be measured using InBody 770 (Biospace).The mean change in HGS from the beginning to weeks 6 and 12 will be measured for all participants. A trained nurse will measure HGS using a digital handheld dynamometer (EH101; Xiangshan, Guangdong, China) to the nearest 0.1 kg according to the recommendation of the Chinese National Physical Fitness Evaluation Standard.^24^ The participants will be asked to perform three measurements for each hand, with rest periods of ≥30 s between each measurement. The HGS will be determined as the maximum value of the six records.The mean change in waist circumference and hip circumference from the beginning to weeks 6 and 12 will be measured for all participants. A trained nurse will measure the waist circumference using a tape at the level mid-way between the lower rib margin and the iliac crest with the participant breathing out gently. Hip circumference will be measured as the maximum circumference over the buttocks.^25^The mean change in physical activity from the beginning to weeks 3, 6, 9 and 12 will be measured for all participants using the self-reported International Physical Activity Questionnaire Short Form (IPAQ-SF).^26^The mean change in the score of the sit-to-stand test from the beginning to weeks 6 and 12 will be measured for all participants. A trained nurse will perform the 30 s sit-to-stand test,^27^ which is a classic test for measuring the performance of lower extremity muscles.The mean change in energy intake from the beginning to weeks 3, 6, 9 and 12 will be measured for all participants using the self-reported Food Frequency Questionnaire (FFQ).^28^The mean change of lipid profiles, fasting glucose, fasting insulin, HOMA-IR and albumin from the beginning to the end of the 12-week intervention will be measured for all participants.

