### Sample size estimation

To date, no studies have been done to determine whether HMB-enriched nutritional supplements are effective and safe for improving muscle mass and muscle function in obese adults during weight loss. To determine the sample size, we examined similar studies on HMB and referred to the study by Peng and Cheng that evaluated the effectiveness of HMB for improving SMM and quality in prefrail older adults.^12^ Using a 0.05 significance level, 80% statistical power and 25% attrition rate, a sample size of 70 has been assumed using an assumed effective size of 0.93. Moreover, to achieve a gender-balanced distribution within and between groups, a random stratification method including 36 samples per gender is proposed, adding up to 72 samples in total.

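### HOMA-IR and fasting insulin are compared as raw mean change without routine baseline adjustment, which loses power if effects are proportional; type I error is unaffected

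*Protocol article*

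**What the plan says.** Under Secondary outcomes, the protocol article defines the metabolic endpoint as "The mean change of lipid profiles, fasting glucose, fasting insulin, HOMA-IR and albumin from the beginning to the end of the 12-week intervention". No log, ratio or percentage scale is mentioned.

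Under Outcomes, "the homeostasis model assessment of insulin resistance (HOMA-IR) will be calculated using the equation" "fasting glucose (mg/dL)×fasting insulin (μIU/mL)/405", so HOMA-IR is a product of two concentrations.

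Under Statistical analysis plan, "We will use the same methods for analysing secondary outcomes as we did for analysing the primary outcome". For the primary outcome, "The independent two-sample t-test or Mann-Whitney U test will be used based on the distributional normality". The rank test is the only remedy named for non-normal data. On covariates: "We will make adjustments based on the covariates if there are significant demographic differences between the groups or if baseline variables differ significantly". The baseline value of the outcome is therefore not routinely in the model. The Discussion adds that physical activity and energy intake will be adjusted for, but neither is the baseline value of the marker being analysed.

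**The concern.** On the log scale HOMA-IR is a sum: ln(HOMA-IR) = ln(glucose) + ln(insulin) − ln(405). A treatment that lowers insulin by a fixed percentage shifts ln(insulin) and ln(HOMA-IR) by a constant. In raw units it produces a larger fall in a participant who starts high than in one who starts low. The between-arm comparison of raw change then carries the baseline spread as extra noise. The Mann-Whitney test does not remove it, because it ranks the same raw differences. Leaving baseline out of the model adds a second, separate loss.

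What is at stake is precision on outcomes that are already being measured, in a trial that calls itself small. Validity is not at stake.

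**Working it through.** **Is there a planned figure to reproduce?** Not for these outcomes. The only calculation is for skeletal muscle mass ("80% statistical power and 25% attrition rate, a sample size of 70 has been assumed", effect size 0.93). With those inputs, two-sided, n per arm = 2(1.96 + 0.8416)²/0.93² = 18.1, so 19 by the normal approximation or 20 by the t-test. That is 40 completers and 40/0.75 = 53.3, rounded up to 54, not 70. The mismatch concerns the primary outcome and does not bear on this point. From that section I take only the completers per arm: 72/2 × 0.75 = 27.

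**Inputs from the protocol:** 1:1 allocation, 72 randomised, 25% attrition, two-sided 0.05, and the tests quoted above.

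**Assumptions (the protocol gives none of these):** log-normal values; log-SD 0.4-0.6; correlation of log baseline with log week-12 value 0.5-0.7; a 15% fall in both arms; a further proportional fall on active.

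**Mechanism.** At log-SD 0.5 the 10th and 90th baseline centiles are exp(∓1.2816 × 0.5) = 0.53 and 1.90 times the median. A 20% fall is then 0.11 units at the low end and 0.38 at the high end.

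**Hand check of the log analyses** (log-SD 0.6, r = 0.7, 25% effect, ln 0.75 = −0.288):
- Log change: SD = 0.6 × √(2 × 0.3) = 0.465; SE = 0.465 × √(2/27) = 0.1265; 0.288/0.1265 = 2.27. Power ≈ Φ(2.27 − 2.007) ≈ 60%.
- Log ANCOVA: SD = 0.6 × √(1 − 0.49) = 0.428; SE = 0.1166; 0.288/0.1166 = 2.47. Power ≈ Φ(2.47 − 2.008) ≈ 68%, slightly optimistic because it ignores chance baseline imbalance.

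**Simulation of all the analyses** (27 per arm, thousands of trials per scenario, error about one point). The planned test is t or Mann-Whitney on raw change, chosen by a Shapiro-Wilk test.

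| log-SD, r, further fall | Planned test | ANCOVA, raw | t-test, log change | ANCOVA, log |
|---|---|---|---|---|
| 0.4, 0.7, 25% | 74% | 92% | 92% | 95% |
| 0.6, 0.7, 25% | 41% | 56% | 60% | 66% |
| 0.5, 0.7, 20% | 38% | 54% | 55% | 61% |
| 0.6, 0.5, 20% | 18% | 29% | 27% | 34% |
| 0.5, 0.7, 10% | 13% | 17% | 17% | 18% |
| no effect | about 5% | about 5% | about 5% | about 5% |

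Over the whole grid with a 20-25% effect, the planned test has about 18-75% power, log change about 25-93% and log ANCOVA about 32-96%. With a 10% effect the log scale alone gains about 2-5 points. Adding log baseline brings the gain to at most about 8 points, at the narrowest spread (17.5% to 25.6% at log-SD 0.4, r = 0.7).

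**Does the rank test repair it?** Only in part. With a 10% common fall, log-SD 0.6, r = 0.7 and a 25% effect, the raw t-test has 37%, Mann-Whitney 43% and log change 61%.

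**Low-spread lipids** (log-SD 0.20 and 0.25, r = 0.7, 10% effect, 10% common fall): raw t-test 59% and 42%, log change 69% and 50%. With baseline in the model the scale hardly matters: raw ANCOVA 74% and 55%, log ANCOVA 75% and 56%.

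**The case against.** The best defence is that nothing here is invalid. A unit difference in mean change is a legitimate estimand, the tests hold their level, and a rank test is offered for skewed data. The scale for individual laboratory markers is often left to an analysis plan, and none is shown. That defence stands on validity. It does not make this a mere omission: the article fixes the change score, the tests, the rule for choosing between them and their transfer to the secondary outcomes. An analysis plan that used logs would depart from that text.

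Three further objections stand and limit the point:
- **Much of the loss comes from the missing baseline covariate, not from the raw scale.** Raw ANCOVA alone recovers (56 − 41)/(60 − 41) = 79% of the gain from log change in the second row of the table, and (54 − 38)/(55 − 38) = 94% in the third. In the fourth row it exceeds log change. A t-test on log change is therefore not the best remedy.
- **The effect size is assumed.** Both arms receive the same calorie-restriction scheme, and nothing in the protocol supports a 20-25% between-arm fall in HOMA-IR.
- **Proportionality is assumed.** If effect and noise are additive, the log scale need not gain anything.

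A reader might also infer that any effect would be swamped by baseline spread, that a few insulin-resistant participants would decide the result, or that all the lipids are affected alike. The documents do not support these readings. They give no distribution for any marker. A history of diabetes is an exclusion, which may narrow the upper tail. At log-SD 0.4 the planned test still has about 74% power for a 25% effect. For low-spread lipids, logs add only about a point once baseline is adjusted for.

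**Conclusion.** The point holds for HOMA-IR and fasting insulin as a loss of efficiency, not as an error of inference. Under proportional effects of 20-25% and the assumptions above, log ANCOVA gains roughly 15 to 30 points of power over the planned test. In the tabulated cases the gains are 95 − 74 = 21, 66 − 41 = 25, 61 − 38 = 23 and 34 − 18 = 16. For a 10% effect the gain is a few points on a power that stays low whichever method is used.

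Triglycerides would be covered only if the lipid profile reports them (the protocol does not name its components) and if they are as skewed as HOMA-IR. There is no case here for changing the scale of glucose, albumin, the other lipids or the bioimpedance outcomes. These are secondary outcomes for which the trial was not sized, so the primary conclusion is unaffected. The change is worth making because it is cheap, not because the plan is unsound.

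**What to change.** In Secondary outcomes and in Statistical analysis plan, prespecify before the treatment codes are broken:

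> HOMA-IR, fasting insulin and, if reported in the lipid profile, triglycerides will be analysed by ANCOVA of the natural log of the week-12 value on treatment group, with the natural log of the baseline value as covariate. The result will be given as a between-arm ratio of geometric means with 95% CI. Raw mean change will be reported descriptively.

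Leave glucose, albumin, the other lipids and the bioimpedance outcomes on their own scale.

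The cost is a sentence or two of text and a change of estimand: the result becomes a ratio rather than a difference in units. No extra participants, visits or assays are needed. The scale must be fixed in advance, since choosing it after seeing the data would be post hoc.
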